#### Illustration of a treatment sequence

[figure not shown]

The quantitative secondary endpoints were :

- the variation (after 2 sessions of 90 min of horticultural therapy versus 2 sessions of 90 min of handiwork) in the level of rumination measured using the self-administered 'Rumination Reflection Questionnaire' (Appendix D) validated in English and translated into French with the help of a professional translator,
- the change (after 2 sessions of 90 min horticultural therapy versus 2 sessions of 90 min handiwork) in the level of dramatization measured by the dramatization sub-score of the self-administered Coping Strategy Questionnaire (Appendix E).

The self-administered 'Rumination Reflection Questionnaire' and 'Coping strategy questionnaire' will be completed by patients:

- before the start of the 1st activity session (1st week: 1st exhibition),
- after the end of the 2nd activity session, during the last activity day of the 1st week (1st exhibition)
- after the end of the 2nd activity session on the last activity day of the 3rd week (3rd week: 2nd exposure).

The qualitative secondary endpoints were patients' opinions of the horticultural therapy and handiwork activities collected at the end of the intervention (during the final evaluation, after the end of the 2nd activity session on the last activity day of the 3rd week) using a standardized self-administered questionnaire with closed questions.

Responses will be expressed using an 11-class Likert scale from 0 to 10) and 1 open-ended question, the answers to which will be expressed in free text (Appendix H).

The thematic analysis of the text will be carried out by 2 independent reviewers.

Other data will be collected (without comparative analysis):

- level of beliefs and expectations regarding treatment (5, no beliefs and expectations, and 45, maximum beliefs and expectations) (Appendix B).
- level of clinically significant depressive symptoms assessed by the depression subscale of the self-administered Hospital Anxiety Depression HADd scale (0, no symptoms and 21, maximum symptoms) (Appendix G).
- level of clinically significant anxiety symptoms assessed by the anxiety subscale of the HADa self-administered scale (0, no symptoms and 21, maximum symptoms) (Appendix G).
- level of fears and beliefs assessed by the self-administered Fear-Avoidance Beliefs Questionnaire (FABQ) work: (0, no fears and beliefs and 24, maximum fears and beliefs) and physical activity: (0, no fears and beliefs and 42, maximum fears and beliefs) (Appendix F).
- variation in the level of activity limitation specific to low back pain, as assessed by the Roland-Morris self-administered questionnaire (0, no limitation, 24, maximum limitation) (Appendix C).
- change in quality of life as assessed by the SF-12 questionnaire (increase in score means improvement in quality of life) (Appendix A).

These questionnaires will be completed by patients:

before the start of the 1st activity session (1st week: 1st exhibition),

after the end of the 2nd activity session, on the last activity day of the 1st week (1st exhibition)

after the end of the 2nd activity session, on the last activity day of the 3rd week (2nd exhibition).

Activities performed during the treatment abstention period will be collected prior to the second treatment sequence (3rd week: 2nd exposure).

Caregivers' opinions on the horticultural therapy and handiwork activities will be collected at the end of the intervention (during the final evaluation, after the end of the 2nd activity session on the last activity day of the 3rd week) by means of a standardized self-administered questionnaire comprising 2 closed questions (for 1 of these questions, answers will be expressed using an 11-

class Likert scale from 0 to 10) and 1 open question whose answer will be expressed in free text (Appendix I).

### Illustration of a treatment sequence

[figure not shown]

## 5 DESCRIPTION OF RESEARCH METHODOLOGY

### 5.1 Experimental design

Pilot randomized controlled cross-over study in the Department of Re-education and Rehabilitation of the Musculoskeletal System and Rachis Pathologies at Hôpital Cochin (Pr [name]) using a mixed methodology (quantitative and qualitative).

Participants will be their own controls and will be randomized in a 1:1 ratio to receive a sequence of treatments involving the experimental intervention (horticulture) in either stage 1 or stage 3, separated by a wash-out stage.

Therapists and participants will not be blinded to the treatment sequence, but the neuroradiologist and biostatistician will be.

### 5.2 Number of participating centers

There is only 1 recruiting center (Service de Rééducation et de Réadaptation de l'Appareil Locomoteur et des Pathologies du Rachis, Hôpital Cochin).

However, another center is associated with this study, the Diagnostic Neuroimaging Department of the Hôpital Sainte-Anne (Pr [name]), where the MRI scans will be performed and analyzed.

#### - Recruiting centers

Service de Rééducation et de Réadaptation de l'Appareil Locomoteur et des Pathologies du Rachis, Hôpital Cochin.

#### - Non-recruiting centers

MRI scans will be carried out in the Diagnostic Neuroimaging Department at Hôpital Sainte-Anne (Pr [name]), 1 km from Hôpital Cochin. Patients will be accompanied on foot by staff from the rehabilitation department.

MRI n°1 will be performed on the 1st day of treatment, before the start of the 1st activity session. MRIs n°2 and n°3 will be performed at the end of the last activity session, at the end of weeks 1 and 3rd respectively.

## 5.3 Description of measures taken to reduce and avoid bias

### 5.3.1 Subject identification

For the purposes of this research, subjects will be identified as follows:  
center no. (3 numeric positions) - person selection order no. in center (3 numeric positions) - initial surname - initial first name

This reference is unique and will be kept for the duration of the research.

### 5.3.2 Randomization

The treatment sequence will be randomly allocated using an interface implemented in Cleanweb software, and will take place in 3 stages over 3 consecutive weeks.

Depending on the group allocated, the treatment sequence will begin with either the experimental intervention (horticulture) or the control intervention (handiwork).

The 3-week period was chosen to minimize the influence of the natural evolution of symptoms on the primary endpoint.

In addition, since each participant is his or her own control, his or her exposome should vary little over this period. Significant changes in exposome will be collected using a checklist. The 1-week wash-out period seems sufficient to allow a return to basal levels of activation of the anterior cingulate cortex in response to each participant's habitual exposome.

## 6 HOW WORKS

| Persons whose consent is sought                                                 | Who informs and obtains the person's consent                                                | When is the person informed?                                                                                          | When is the person's consent obtained?                                                                                                         |
|----------------------------------------------------------------------------------------|----------------------------------------------------------------------------------------------------|------------------------------------------------------------------------------------------------------------------------------|-------------------------------------------------------------------------------------------------------------------------------------------------------|
| 

the person carrying out the research ;

 | 

the principal investigator, co-investigator

 | 

when selecting "telephone screening

and again at the inclusion visit

 | 

consent is obtained at the time of the inclusion visit, after a minimum reflection period of one week

 |

Example of the treatment sequence starting with the control intervention :

- Stage 1 (1st week: 1st exposure period: do-it-yourself): on the 1er day of treatment, before the start of the 1st activity session: participants will undergo a brain MRI in the Diagnostic Neuroimaging department at Hôpital Sainte-Anne (Pr [name]) (MRI n°1). During this week, participants will have 2 activity sessions (crafts) lasting 90 minutes, led by an occupational therapist with experience of this activity with people suffering from chronic low back pain, and taking place in the occupational therapy room (in the basement of the Hardy building). At the end of the last activity session (handiwork) of the 1st week, participants will undergo a new brain MRI (MRI n°2) in the Diagnostic Neuroimaging department of the Hôpital Sainte-Anne. The time between the end of the activity and the MRI will be a maximum of 3 hours. Patients will be accompanied on their journey between the Cochin and Sainte-Anne hospitals by a nurse from the Cochin hospital rehabilitation department.

- Stage 2 (week 2: wash-out period): no activities will be organized during this week. Participants will continue with their usual daily activities.

- 3rd stage (3rd week: 2nd exposure period: horticulture): participants will have 2 sessions of 90-minute horticultural therapy activities, led by an occupational therapist with experience of this activity with chronic low-back pain sufferers, and taking place in the green outdoor premises of Hôpital Cochin. The department has purchased a greenhouse to enable the horticultural

activity to continue whatever the weather conditions. At the end of the last horticultural workshop, participants will undergo a final brain MRI (MRI n°3). The time between the end of the activity and the MRI will be a maximum of 3 hours. Patients will be accompanied on their journey from Hôpital Cochin to Hôpital Sainte-Anne by a nurse from the Cochin rehabilitation department.

### Illustration of a treatment sequence

[figure not shown]

## 6.1 Research calendar

|                                               |                                   |
|-----------------------------------------------|-----------------------------------|
| Maximum time between selection and inclusion  | 1 month                           |
| Length of inclusion period                    | 12 months                         |
| Duration of subject participation, of which : |                                   |
| Duration of intervention                      | 3 weeks                           |
| Follow-up time                                | No follow-up outside intervention |
| Total research time                           | 13 months                         |

### 6.1.1 Selection visit

The doctor asks the patient if he or she agrees to be contacted by telephone to participate in a study... If the patient agrees, the doctor puts him or her on a list.

Selection: patients on the list are called by the investigator (or a Clinical Study Technician (CST)). During this telephone interview, patients are informed of the objectives and content of the study. If patients agree to take part, an inclusion visit is scheduled (within a minimum of one week (cooling-off period) and a maximum of one month).

### 6.1.2 Inclusion visit

The investigator responsible for inclusion will check the inclusion criteria, inform the patient of the objectives of the study using an information note, collect the patient's written consent, collect the data, randomize the patient using a website dedicated to the study (e-CRF Cleanweb, Télémédecine company), and inform the patient of his or her appointments according to the allocated allocation group.

#### Collection of socio-demographic and professional characteristics :

- surname, first name, date of birth (partially entered, only month and year of birth will be shown), postal address and e-mail address,

– size, weight

– professional information:

- level of education, last occupation
- Satisfaction with current job
- Past work stoppages due to low back pain
- Number and duration of days off work since onset of low back pain non-specific
- Number of days off work in the last year
- Low back pain related to a work accident :
  - if yes: date of accident :
- Low back pain linked to an occupational disease
  - if yes: date of onset of occupational illness :

– Sports activities :

- Volume of weekly sports activities (end date, if applicable)
- Current impact of low back pain on your sporting activities

Collection of clinical characteristics :

- Date of onset of low back pain
- Start date of current episode
- Taking painkillers and NSAIDs (non-steroidal anti-inflammatory drugs)

Self-administered questionnaires: at the beginning of 1st exposure, before the start of the 1st activity session.

–Rumination level assessed by the Rumination Reflection Questionnaire (0: no rumination and 60: maximum rumination)

–Level of dramatization assessed by the dramatization sub-score of the self-administered Coping Strategies Questionnaire (CSQ) (0, no dramatization, 20, maximum dramatization).

Collection of MRI characteristics (MRI no. 1): blood perfusion of the anterior cingulate cortex (in ml/100 g tissue/min): at the start of the 1st exposure, before the start of the 1st activity session.

Sequences used :

- high-resolution T1-weighted image for anatomical reference (Canon sequence: 3D FAST FE, equivalent to MPRAGE)
- ASL, perfusion-weighted image (Canon sequence: ASTAR)
- PD, proton density-weighted image for quantitative CBF measurement (Canon sequence: ASTAR, with long TR)

Injection of contrast media: none

### 6.1.3 Research follow-up visits

No follow-up outside intervention

Self-administered questionnaires: at the end of 1st exposure and at the beginning of 2nd exposure

–Rumination level assessed by the Rumination Reflection Questionnaire (0: no rumination and 60: maximum rumination)

–Level of dramatization assessed by the dramatization sub-score of the self-administered Coping Strategies Questionnaire (CSQ) (0, no dramatization, 20, maximum dramatization).

Collection of MRI features (MRI no. 2): blood perfusion of the anterior cingulate cortex (in ml/100 g tissue/min): at the end of the 1st exposure, after the third activity session.

### 6.1.4 End of research visit

End of research equals end of intervention

Self-administered questionnaires: at the end of the 2nd exhibition, after the last activity session:

–Rumination level assessed by the Rumination Reflection Questionnaire (0: no rumination and 60: maximum rumination)

-Level of dramatization assessed by the dramatization sub-score of the self-administered Coping Strategies Questionnaire (CSQ) (0, no dramatization and 20, maximum dramatization).

Collection of MRI features (MRI no. 3): blood perfusion of the anterior cingulate cortex (in ml/100 g tissue/min): at the end of the 2nd exposure, after the end of the last activity session.

Sequences used :

- high-resolution T1-weighted image for anatomical reference (Canon sequence: 3D FAST FE, equivalent to MPRAGE)
- ASL, perfusion-weighted image (Canon sequence: ASTAR)
- PD, proton density-weighted image for quantitative CBF measurement (Canon sequence: ASTAR, with long TR)

Injection of contrast media: none

No medical follow-up is planned at the end of the study. Patients will be monitored as planned by the referring physician.

Group analysis :

- Correction of ASL data movements (with FSL's BASIL toolbox)
- Quantification of cerebral blood flow = CBF (with FSL's BASIL toolbox)
- Calculation of the ASL image transformation on the anatomical image (with ANTs software)
- Calculation of anatomical image transformations on a standard space, e.g. ICBM152 (with ANTs software)
- Applying these transformations to IVC maps
- Extraction of IVC values from an atlas (DKT) and statistical analysis of standardized IVC maps.

## 6.2 Summary table or diagram of research chronology

|                                                                   | Selection
S-4 to S-1 | Inclusion and
randomization
S 0 | Start of
intervention
S+2 to S+4 | End of 1 st
exhibition
S+3 to S+5 | Start of 2 nd
exhibition
S+5 to S+7 | End of 2 nd
exhibition:
S+6 to S+8 |
|-------------------------------------------------------------------|-------------------------|---------------------------------------|----------------------------------------|----------------------------------------------------|------------------------------------------------------|-----------------------------------------------------|
| Information                                                       | ✓                       | ✓                                     |                                        |                                                    |                                                      |                                                     |
| Written consent                                                   |                         | ✓                                     |                                        |                                                    |                                                      |                                                     |
| Randomization                                                     |                         | ✓                                     |                                        |                                                    |                                                      |                                                     |
| Clinical
examination                               |                         | ✓                                     |                                        |                                                    |                                                      |                                                     |
| Paraclinical
examinations (and
questionnaires)  |                         |                                       | ✓                                      | ✓                                                  | ✓                                                    | ✓                                                   |

Clinical examination:

Collection of clinical characteristics

- date of onset of low back pain
- start date of current episode
- taking painkillers and NSAIDs (non-steroidal anti-inflammatory drugs)

Para-clinical examinations :

- Self-administered questionnaires: at the start of the 1st exposure, before the start of the 1st activity session.

- Rumination level assessed by the Rumination Reflection Questionnaire (0: no rumination and 60: maximum rumination)
- Level of dramatization assessed by the dramatization subscore of the self-administered Coping Strategies Questionnaire (CSQ) (0, no dramatization, 20, maximum dramatization).
- Collection of MRI features (MRI no. 1): blood perfusion of the anterior cingulate cortex (in ml/100 g tissue/min)

### 6.3 Distinction between care and research

| Research interventions | Acts, procedures and treatments related to care | Acts, procedures added by search                                                                                                                                                                                                                                                                                                   |
|------------------------|--------------------------------------------------------|-------------------------------------------------------------------------------------------------------------------------------------------------------------------------------------------------------------------------------------------------------------------------------------------------------------------------------------------|
| Consultations          | NA                                                     | Inclusion visit                                                                                                                                                                                                                                                                                                                           |
| Imaging                | NA                                                     | MRI and self-administered questionnaires:
- at the start of the 1 st exhibition, before the start of the 1 st activity session.
- at the end of the 1 st show and at the beginning of the 2 nd show
- at the end of the 2 nd exhibition, after the last activity session. |

## 7 SELECTION CRITERIA

### 7.1 Inclusion criteria

- Adult patients  $\geq 18$  years,
- Chronic non-specific low back pain (current episode lasting  $\geq 3$  months),
- Indication for rehabilitation
- Failure of 1st line treatment,
- Up-to-date DTP (diphtheria tetanus poliomyelitis) vaccination,
- Patients able to walk 2 km,
- Membership of a social security scheme or beneficiary
- Signature of consent to participate.

### 7.2 Non-inclusion criteria

- Specific low back pain,
- MRI contraindications (metallic equipment, pacemaker, cochlear and intraocular metallic implants, current pregnancy, uncontrollable claustrophobia)
- Current work stoppage or work stoppage of more than 3 months in the last year,
- No paid employment
- Insufficient command of the French language,
- Participation in another research project on low back pain
- Patients under guardianship or curatorship,
- Patients on AME (State medical Aid).

### 7.3 Recruitment procedures

*Justification of recruitment capacity with regard to the number of subjects to be included ;*

A difference of 7 ml/100 g tissue/min (SD=4) between perfusion changes in the anterior cingulate cortex after the 2 horticultural therapy sessions and after the 2 handiwork sessions is estimated to be clinically relevant (Bratman et al., 2015). Given this expected difference, a risk  $\alpha$  of 5%, a power of 90%, and a potential lost to follow-up of 20%, we planned to include a total of 16 patients.

Participants will be recruited from among patients seen in consultation by a doctor in the department or a doctor attached to the department. Participants will also be informed of the study by means of posters displayed in the Department of Re-education and Rehabilitation of the Musculoskeletal System and Spine Pathologies at Cochin Hospital, and in the waiting rooms of the private practices of doctors attached to the department (Appendix J and K). A patient included in the study will be able to call on his or her own network of acquaintances (recruitment based on the snowball effect). In the department it is during a consultation that the physician (-investigator) asks the patient if he or she agrees to be contacted by telephone about a study.

|                                                   | Number of subjects |
|---------------------------------------------------|---------------------------|
| Total number of subjects selected          | 16                        |
| Number of recruiting centers               | 1                         |
| Inclusion period (months)                  | 12                        |
| Number of subjects / center                | 16                        |
| Number of subjects / center / month | 1,3                |

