| Number of subjects selected                       | Sample size is estimated at 16 participants. We predict a mean difference in variation in anterior cingulate cortex blood perfusion of 7 ml/100 g tissue/min with a standard deviation of 4, a power of 90%, an $\alpha$ risk of 5% and a potential lost to follow-up of around 20%.                                                                                                                                                                                                                                                                                                                                                                                                                                                                                                                                                                                                                                                                                                                                                                                                                                                                                                                                                                                                                                                                                                                                                                                                                                                                                                                                                                                                                                                                                                                                                                                                                                                                                                                                                                                                                                                                                                                                                                                                                                   |

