## **13 STATISTICAL ASPECTS**

Intention-to-treat study

Quantitative variables will be described by their means and standard deviation, and qualitative variables by their absolute and relative frequencies.

Depending on the normality of the distribution of the quantitative variables of interest, they will be compared using a rank comparison test (Wilcoxon test) or a mean comparison test (Student's t-test for paired samples).

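### The planned 16 patients and 90% power do not follow from the stated inputs under the planned paired test, which needs about 8 with 20% loss

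*Protocol*

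**What the plan says.** The synopsis opens its sample-size line with "Sample size is estimated at 16 participants" and gives the inputs: "We predict a mean difference in variation in anterior cingulate cortex blood perfusion of 7 ml/100 g tissue/min with a standard deviation of 4", with 90% power, a 5% alpha risk and around 20% lost to follow-up. Section 7.3 repeats them, starting from "A difference of 7 ml/100 g tissue/min (SD=4) between perfusion changes in the anterior cingulate cortex" and ending with "a power of 90%, and a potential lost to follow-up of 20%, we planned to include a total of 16 patients".

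The design and test are also fixed. Section 5.1 says: "Participants will be their own controls and will be randomized in a 1:1 ratio to receive a sequence of treatments". Section 13 and the synopsis plan either a Wilcoxon test or a "Student's t-test for paired samples", depending on normality.

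The protocol does not give the sample-size formula, the sidedness of the 5%, the number needed before loss, or a within-patient correlation.

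**The concern.** A standardised paired difference of 7/4 = 1.75 is very large, and a paired test needs only a handful of patients to detect it. Sixteen is about twice what the inputs call for, so either the formula does not match the analysis or the SD is not the one the text names.

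At stake is what the trial is said to be able to show. The inputs, the test, the 90% and the 16 cannot all be true together. A reader cannot tell whether the sponsor expects an SD of 4, in which case differences well below 7 are detectable, or an SD nearer 7, in which case 16 is about right. Anyone using this pilot to plan a later trial meets the same ambiguity.

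**Working it through.** **Inputs.** Difference 7, SD 4, alpha 5%, power 90%, loss 20% (synopsis; Section 7.3). Paired analysis of a cross-over (Sections 5.1 and 13). Sidedness is not stated; two-sided is assumed unless noted. Loss is applied as n/0.80, rounded up. Sixteen enrolled with 20% loss leaves 16 × 0.8 = 12.8, so 12 to 13 completers.

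**Step 1: can 16 be reproduced with the planned test?** The paired t-test has n − 1 degrees of freedom and non-centrality √n × 7/SD_diff.

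*SD 4 as the SD of the within-patient difference (the literal reading):*

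| Completers | Power |
|---|---|
| 5 | 82.8% |
| 6 | 92.3% |
| 12 | 99.98% |
| 13 | 99.99% |

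So 6 completers are enough, and 6/0.8 = 7.5, or 8 enrolled.

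Variants on the same reading:
- Normal approximation: ((1.960 + 1.282) × 4/7)² = 3.43, so 4, or 5 with loss.
- Cross-over t with a period term (N − 2 degrees of freedom): 6 gives 88.6% and 7 gives 95.4%, so 7, or 9 with loss.
- Exact signed-rank test by simulation: 79% at 6 and 95% at 7, so 7, or 9 with loss.
- One-sided paired t: 5, or 7 with loss.

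*SD 4 as the SD of each change:* SD_diff = 4√(2(1 − ρ)).

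| ρ | SD_diff | Completers | With 20% loss |
|---|---|---|---|
| 0 | 5.66 | 10 (93.5%; 9 falls just short of 90%) | 13 |
| 0.25 | 4.90 | 8 | 10 |
| 0.5 | 4.00 | 6 | 8 |

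None of these gives 16.

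**Step 2: what would make 16 right for a paired test?** For 12 to 13 completers to be what 90% power requires, SD_diff must be about 6.8 to 7.1. If 4 is the SD of each change, then ρ = 1 − SD_diff²/(2 × 16), which is 1 − 6.8²/32 = −0.45 to 1 − 7.1²/32 = −0.58. Both changes subtract the same MRI #1 (Section 4.1), which pushes their correlation upward, so a negative value of that size would need its own justification.

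**Step 3: which formulas do reach 16?** Those that ignore the pairing.
- Unpaired two-sided t, non-centrality (7/4)√(n/2): 7 per group gives 85.2% and 8 per group gives 90.2%. The total is 16 before loss and 20 with loss.
- Unpaired one-sided normal: 2 × ((1.645 + 1.282) × 4/7)² = 5.6, so 6 per group; 6/0.8 = 7.5, so 8 per group, or 16 with loss.
- Unpaired two-sided normal: 2 × 3.43 = 6.86, so 7 per group, or 14; 14/0.8 = 17.5, or 18 with loss.

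**Step 4: what do 12 to 13 completers give?**

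| Completers | Difference at 90% power, SD_diff 4 | Largest SD_diff for 90% power at 7 |
|---|---|---|
| 12, paired t | 4.12 | 6.8 |
| 13, paired t | 3.92 | 7.1 |
| 12, period term | 4.16 | 6.7 |
| 13, period term | 3.97 | 7.1 |

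**The case against.** The strongest reply is that nothing is lost. The discrepancy makes the trial larger than its inputs require, the study calls itself a pilot, and spare precision is sensible when the SD is uncertain. That stands as far as the patient number goes, and it is why the fix leaves 16 alone. It does not make the power statement correct.

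A second reply is that patients attend in groups of 4 (synopsis; Section 2.4), and 13 rounded up to whole groups is 16. This is possible, but the protocol does not give it as a basis for the number. It also needs the zero-correlation reading, which departs from the wording: both places attach the SD to the difference between the changes.

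A third is that the Wilcoxon branch needs more patients. It does, but only about 9 with loss.

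Several stronger readings are tempting and are not supported:
- *That the sponsor used an unpaired formula.* The arithmetic is consistent with this, but no formula is stated and more than one unpaired route reaches 16.
- *That no reading at all gives 16 with loss included.* The one-sided unpaired normal formula does, and sidedness is unstated. The defensible statement concerns the planned paired test.
- *That the cited trial in healthy volunteers offers no within-patient SD.* The protocol describes that trial only briefly, and what SDs it reports cannot be checked here.
- *That the trial is underpowered, or that a null result is bound to be misread.* At the stated inputs power is far above 90%, and interpretation would also rest on the estimate and its interval.

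**Conclusion.** The point holds. The stated inputs do not lead to 16 under the planned test, and the stated 90% is not that test's power. On the literal reading the excess is twofold (16 against 8); on the least favourable reading checked, with uncorrelated changes, it is 16 against 13. The conclusion rests on a two-sided 5% level, approximately normal differences for the t-test figures, and 20% loss applied as division by 0.80. A one-sided paired test would widen the gap. The error is conservative and lies in the justification, not in the feasibility of the trial, so it should be corrected but does not call the design into question.

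**What to change.** Keep 16 and rewrite the sample-size sentence in Section 7.3 and the matching synopsis line so that they:
- name the two-sided paired cross-over test as the basis;
- confirm that SD 4 is the SD of the within-patient difference between the two changes, or else give the single-change SD and the assumed correlation;
- give the number required before loss as well as after, and say on what grounds 16 was chosen if it exceeds that number;
- state what 12 to 13 completers provide: 90% power for a difference of about 3.9 to 4.2 ml/100 g/min at SD 4, or for 7 with a paired-difference SD up to about 6.7 to 7.1.

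Whether to describe 7 as an assumed effect instead of a clinically relevant one is optional and separate from the arithmetic.

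The cost is rewording in two places. No patients are added, and the visits and the analysis do not change.
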